## Abstract

**Purpose:**

The long-term objective of the Ablation-IMaging and Advanced Guidance for workflow optimization in Interventional Oncology (A-IMAGIO) project is to develop a standardized, accessible, low-complex, high-precision, end-to-end solution for treatment planning, needle guidance, and treatment evaluation for thermal liver ablation.

**Materials and Methods:**

This is a prospective, international, multicentre, observational registry study. Patients will be included with age ≥ 18 years, diagnosed with primary or secondary liver tumours, and undergoing thermal liver ablation. A detailed dataset of medical history, baseline clinical and imaging parameters, tumour characteristics, ablation technique/parameters, treatment outcomes, periprocedural images, and adverse events, will be collected for all participants. This data will be used to develop AI algorithms for prognostic modelling and quantitative imaging analysis. Additionally, costs associated with thermal liver ablation clinical pathway will be evaluated.

**Expected Gain of Knowledge:**

The results of this registry study are expected to provide profound insight in current variability among centres in performing thermal liver ablation, and identify best practices in order to eventually facilitate standardization and universally excellent clinical outcomes.

**Trial Registration:**

National Institute of Health Clinical trial database (NCT06179602) https://clinicaltrials.gov/study/NCT06179602.

**Graphical Abstract:**

[figure not shown]

**Supplementary Information:**

The online version contains supplementary material available at 10.1007/s00270-025-04093-9.

## Introduction

For both primary and secondary liver tumours, thermal liver ablation (TLA) (i.e. RFA and MWA) has proved to be an effective minimally invasive treatment, associated with a low complication rate [1–4]. According to the Barcelona Clinic Liver Cancer (BCLC) staging system, percutaneous TLA is recommended as first-line therapy in patients with very early-stage (0) and early-stage (A) hepatocellular carcinoma (HCC) by the European Association for the Study of the Liver (EASL) and European Society of Medical Oncology (ESMO) guidelines [5, 6]. In oligometastatic colorectal liver metastases (CRLM) up to 3 cm, overall survival (OS) after TLA is non-inferior to surgical resection while offering the advantage of lower complication rates and shorter hospital admissions [7]. Despite the growing evidence demonstrating the efficacy and safety of TLA, there is still a certain resistance to incorporate TLA into clinical guidelines as the treatment of first choice. This is primarily due to scarcity of large-scale high-quality clinical trials comparing TLA to surgical resection. For secondary liver tumours other than CRLM, outcomes of TLA have only been documented in case reports, case–control studies, and retrospective studies, with an absence of large-scale prospective data [8–11].

Alongside the more prominent application of TLA, a wide variety of advanced software tools has become available to improve treatment planning, tumour targeting, and assessment of immediate and long-term treatment response. In recent years, artificial intelligence (AI) models for planning and evaluation have gained interest, as they can aid in improving workflows in different clinical settings. Although these technical advancements were expected to deliver consistent outcomes with minimal operator dependency, they are still not widely used and have paradoxically led to greater diversity in workflow practices [12, 13]. The consequence of this treatment and workflow variability imposes the risk of being followed by inconsistency in clinical outcomes among treating physicians and centres. This variability hampers implementation of TLA as standard of care. For this reason, the European Union funded, A-IMAGIO (Ablation-IMaging and Advanced Guidance for workflow optimization in Interventional Oncology) project was initiated. One of the main goals of the A-IMAGIO project is to expedite the adoption and acceptance of multimodality ablation therapy as treatment of first choice for primary and secondary liver tumours by optimizing treatment workflow and reducing treatment variability.

Within the A-IMAGIO study, data are collected from various centres to gain insight into inter-centre treatment variability and outcomes. This knowledge will be used to identify best practices and techniques and eventually develop a standardized and optimal workflow for TLA.

To support and improve this, clinical and imaging data will be used to develop and validate machine learning and deep learning (DL) based models that allow software-based treatment planning, needle guidance, and assessment of treatment effect.

## Materials and Methods

### Trial Design and Study Setting

This prospective, international, multicentre registry study is coordinated by Leiden University Medical Centre (The Netherlands) and Maastricht University Medical Centre + (The Netherlands). Participating centres include Radboud University Medical Center (The Netherlands), Amsterdam University Medical Centre (The Netherlands), Istituto Nazionale dei Tumori di Milano (Italy), University Hospital of Innsbruck (Austria), Lausanne University Hospital (Switzerland), University Medical Centre Utrecht (The Netherlands), Henri Mondor University Hospital (France), and Newcastle Freeman Hospital (UK). Other centres will be welcome and/or invited to participate.

A detailed overview of the collected data concerning patient and tumour characteristics, ablation technique, and treatment outcomes is described in supplementary 1. Additionally, imaging data will be collected on treatment planning, assessment, and follow-up. To expand the database, retrospective data and data obtained from previously conducted or ongoing prospective studies on TLA of primary and secondary liver tumours will be used [14–16].

### Participants

Table 1 shows the in- and exclusion criteria for participation. For study participation, informed consent will be obtained.

**Table 1 Tab1:** In- and exclusion criteria

Inclusion criteria	Exclusion criteria
Age of 18 years or above Candidate for percutaneous thermal liver ablation, as discussed in a multidisciplinary tumour board Signed informed consent	Patients lacking the capacity to give informed consent

### Intervention

To provide the opportunity to assess current practice, and techniques, identify areas of heterogeneity and identify best practices, patients will undergo percutaneous TLA as standard of care of the participating centre. The procedure is allowed to be performed under general anaesthesia or deep sedation, and the choice of ablation method (MWA or RFA), apparatus, ablation settings, and image guidance techniques for needle placement is also left to the discretion of the treating physician. All patients will undergo a dual-phase contrast-enhanced (cone-beam) CT scan with at least an arterial and portovenous phase immediately before and after the procedure. Contrast can be administered either intravenously, or through a catheter in the hepatic artery, also known as CT hepatic arteriography. Assessment of technical success (i.e. complete eradication of the tumour with sufficient ablation margin) can be evaluated by visual assessment, image co-registration software, and/or confirmation software. As standard of care, a circumferential minimal ablation margin (MAM) of at least 5 mm is generally aimed for.

### Follow-Up

Follow-up will be conducted according to the standard of care of the participating centre. In general, the follow-up of TLA encompasses physical blood tests and imaging such as (CE)CT, MRI, and/or PET-CT, scheduled at three to 6 months intervals. Patients will be monitored for 5 years following inclusion in the study. Follow-up scans will be reviewed by an experienced radiologist, as per standard of care.

### AI Models Development

#### Ablation Margin Assessment

Accurate segmentation of tumour and ablation zones, along with co-registration of pre- and post-ablation CT scans, is essential for ablation margin assessment, such as calculating the MAM. To automate this process, DL-based segmentation models will be developed using multicentre data, with expert segmentation of the tumours and ablation zones serving as ground truth for model training and validation. Two experienced interventional radiologists will independently segment the tumours and ablation zones on the pre- and post-ablation CT scans, respectively. Subsequently, pre- and post-ablation CT scans will be automatically co-registered by aligning liver contour and/or vessel segmentation masks, with manual adjustments made if needed.

#### Prognostic Model for Early Recurrence

Prognostic models will be developed for prediction of early recurrence following TLA for both primary and secondary liver tumours. Potential predictive imaging features will be identified through radiomics-based and DL-based extraction of contrast-enhanced CT scans, with liver, tumour, and ablation zone segmentation. Clinical factors will be identified by uni- and multivariate cox regression analysis. The potential factors will be evaluated for their predictive value, and the selected prognostic biomarkers will be combined as inputs for the prognostic model.

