#### Data Handling

Data from the participating centres will be split into training, validation, and test sets to evaluate model performance. The training and validation sets will serve model development, including hyperparameter optimization and iterative refinements, while the test set will be held out to provide an unbiased estimate of the final model accuracy. In addition, an external validation cohort from a separate clinical centre will further assess the generalizability of the models.

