### Sample Size

The sample size was not predetermined, as this is a registry study. However, approximately 1200 patients are expected to be required for development of aforementioned AI algorithms. Prospective inclusions began on January 17th 2024. This project is designed to continuously include new patients providing an ongoing source for studies aimed at optimizing clinical outcomes of TLA.

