### Statistical Analysis

Descriptive findings will be summarized with means and standard deviations (SD). Continuous variables will be presented with means and SD or ranges for nonparametric distributions. Categorical variables will be shown as numbers and percentages. Kaplan–Meier estimates will be used to assess local and overall recurrence, DFS, and OS. Logistic and Cox regression analyses will be performed to determine predictors for local and overall recurrence, DFS, and OS. The methods used for feature selection and model generation will be based on the extent of data availability. Data will be analysed using R (version 4.2.1; R Core Team, 2023, Austria). Cost of clinical pathway of TLA will be analysed using IBM SPSS Statistics (version 29, IBM, Armonk, USA).

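### Selecting clinical predictors for the early-recurrence model by univariable and multivariable Cox regression, with no shrinkage named, risks losing true predictors and overstating risk differences

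*Protocol article*

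**What the plan says.** The protocol article, section Prognostic Model for Early Recurrence, sets the aim: "Prognostic models will be developed for prediction of early recurrence following TLA for both primary and secondary liver tumours". Imaging inputs come from one route: "Potential predictive imaging features will be identified through radiomics-based and DL-based extraction of contrast-enhanced CT scans". Clinical inputs come from another: "Clinical factors will be identified by uni- and multivariate cox regression analysis". The two are then joined: "The potential factors will be evaluated for their predictive value, and the selected prognostic biomarkers will be combined as inputs for the prognostic model". No significance threshold, order of steps, shrinkage or final model type is given.

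On size, the Sample Size section says "The sample size was not predetermined, as this is a registry study", and adds that "approximately 1200 patients are expected to be required for development of aforementioned AI algorithms". That figure covers all the algorithms together.

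The Data Handling section says "Data from the participating centres will be split into training, validation, and test sets to evaluate model performance". It assigns development and tuning to the training and validation sets, holds the test set back, and adds an external cohort from another centre. The Statistical Analysis section adds a general statement: "The methods used for feature selection and model generation will be based on the extent of data availability".

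**The concern.** This is a method the article states, not a detail it leaves out. Cox regression, univariable and multivariable, is the only route it names for clinical predictors.

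If *identified* means retained because statistically significant, three things follow:

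- A factor that matters only after adjustment can be discarded at the univariable step.
- With few events, many true but moderate predictors fail the threshold by chance.
- Those that pass do so partly because their estimates came out large, so the retained coefficients are biased away from zero. Without shrinkage, predictions for new patients are then too spread out.

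Calibration matters here. Outcome prediction is among the article's primary outcomes, and the section Expected Gain of Knowledge intends the prognostic models to support individualised treatment. A model that ranks patients adequately but exaggerates the differences between them serves that purpose poorly.

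**Working it through.** **The plan's own figure.** The 1200 cannot be reproduced. The article gives no event rate, number of candidates, expected fit or target shrinkage. Everything below therefore rests on assumed inputs, varied over a range.

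**Check 1: how many candidate parameters the numbers support.** The shrinkage criterion for prediction models is

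n = P / [(S − 1) · ln(1 − R²/S)],

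where P is the number of candidate parameters. Assumptions: target shrinkage S = 0.9, and R² = 15% of its maximum, with R²max = 1 − exp{2[φ ln φ + (1 − φ) ln(1 − φ)]} for event proportion φ (a binary approximation).

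- φ = 0.10: R²max = 0.478; R² = 0.0717; ln(1 − 0.0717/0.9) = −0.0830. Patients per parameter = 1/(0.1 × 0.0830) ≈ 120.4. Fifteen candidates need 15 × 120.4 ≈ 1807.
- φ = 0.30: R²max = 0.705; R² = 0.1058; ln(1 − 0.1058/0.9) = −0.1251. Patients per parameter ≈ 80.0. Fifteen candidates need 1200.

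| Candidates | 10% events | 20% | 30% | 40% |
|---|---|---|---|---|
| 15 | 1807 | 1347 | 1200 | 1141 |
| 30 | 3614 | 2694 | 2400 | 2281 |
| 50 | 6023 | 4490 | 3999 | 3801 |

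So 1200 patients, all in development, suffice for about 15 candidates only at 30% events or more. At 10% events they support just under 10 (1200/120.4). An assumed 60% training share (0.60 × 1200 = 720) supports just under 6.

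**Check 2: calibration after screening.** The simulation used univariable p < 0.05, then multivariable p < 0.05, then an unpenalised Cox fit. Settings: 15 or 30 candidates, 6 of them true; pairwise correlation 0.2; SD of the true linear predictor 0.5 or 0.8; 120 replicates per setting. The slope is measured against the true model, and a value below 1 means predictions are too extreme. The ranges are mean slopes across the four settings in each cell. The 300 row stands for an assumed small tumour-type stratum.

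| Patients in development | 10% events | 20% | 40% |
|---|---|---|---|
| 1200 | 0.71–0.90 | 0.85–0.95 | 0.92–0.97 |
| 720 | 0.61–0.83 | 0.73–0.91 | 0.88–0.96 |
| 300 | 0.33–0.67 | 0.54–0.80 | 0.73–0.89 |

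Replicates in which screening retained nothing are left out of these means. At 10% events this was up to 21 of 120 at 1200 patients and up to 42 of 120 at 720.

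To read the slopes: a predicted hazard ratio of 3 between two patients corresponds to a true one of about 3^0.71 ≈ 2.2 at slope 0.71, but 3^0.97 ≈ 2.9 at slope 0.97.

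At 1200 patients, screening kept on average 1.5 to 3.3 of the 6 true predictors with 120 events, and 4.2 to 5.4 with 480.

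**Check 3: is screening or the lack of shrinkage the main fault?** At 1200 patients, fitting all candidates without screening or shrinkage gave slopes of 0.47 to 0.95, worse than screening. Adding a uniform shrinkage factor gave 0.99 to 1.07. At 720 it gave 0.95 to 1.31. The values furthest above 1 came with only 72 events, where the shrinkage factor is itself unstable.

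**Check 4: discrimination.** A separate simulation used a logistic proxy with 720 training patients, 10% events, 8 true predictors among 20 to 40 candidates, correlation 0.3 and 150 replicates. Screening gave an AUC of 0.69 to 0.70 in new patients, with slopes of 0.81 (20 candidates) and 0.65 (40). Ridge gave an AUC of 0.70 to 0.72 and slopes of 1.07 to 1.11. The gain in AUC is about 0.01 to 0.02.

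**The case against.** The strongest reply is that the article does not describe the model simulated here. It states no p-value rule and does not say that one Cox step follows the other. It leaves the type of final model open, mentions hyperparameter tuning, and ties feature selection to the data available. A penalised final model is not excluded. Size is also open: inclusion continues, and retrospective and earlier prospective data will be added. All of this stands, and it limits the point to a risk of unknown size. It does not remove the point, because the general statement on data availability neither withdraws the named Cox step nor offers an alternative. Penalising only the survivors of a screen would also not recover predictors already dropped.

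A reader might infer two stronger faults that the article does not support:

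- **Leakage into the test set.** Data Handling stands under the same AI heading as the prognostic model and assigns model development to the training and validation sets. Choosing inputs is part of development, so the natural reading confines it there. The regression analyses in Statistical Analysis are not said to supply inputs to the AI model.
- **A screen on five years of recurrence.** The Follow-Up section's five years describe patient monitoring. No time window is given for the Cox step, and censoring at an early horizon is equally compatible with the text.

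The held-out set and external cohort are real safeguards: they would show poor calibration if it is assessed. They would not prevent or repair it.

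**Conclusion.** The concern holds as a risk. The article names a Cox selection step for clinical predictors and no shrinkage. On the usual reading, every simulated setting gave a mean calibration slope below 1 and lost some true predictors. The effect runs from serious at 10% events to minor at 40% with 1200 patients. It grows as the development set shrinks, through the data split or through separate models by tumour type.

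The article does not support saying that the model will be miscalibrated at the planned size. No size was formally planned, and the event rate, candidate number, threshold, training share and final model type are all assumptions here. Nor would removing the screen be enough, since the missing shrinkage is the larger fault. The case rests on calibration and lost predictors, not on discrimination. The change is worth making because it is cheap and bears on a primary outcome.

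**What to change.** In Prognostic Model for Early Recurrence, replace the sentence on clinical factors with:

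> Candidate clinical predictors will be prespecified from clinical knowledge, limited to the number the observed events support, and entered together in a penalised (ridge or elastic-net) Cox model with follow-up censored at the early-recurrence horizon; univariable results will be descriptive only.

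If wished, add to Data Handling that feature selection is part of the model development confined to the training and validation sets. This only makes the existing intention explicit.

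The cost is wording and standard software. The downside is that there will be no short list of significant factors to report. The limit on candidates should stay even with a penalty, because shrinkage is itself poorly estimated when events are few.

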#### Treatment Planning Model

To determine the optimal trajectory and number of needles required for effective TLA, a planning model will be developed incorporating key tumour and liver tissue characteristics, such as tumour type, size, shape, location, and liver tissue composition. A segmentation model will be used to accurately delineate liver, tumour, and blood vessels, to identify safe needle trajectories. This model will be trained and validated using preprocedural CT scans containing ground-truth annotations for liver, tumour, and blood vessels, as provided by the experienced interventional radiologists mentioned above. Machine learning models will be developed to recommend the most effective ablation settings. These models, using clinical and imaging data from past treatments, will dynamically adjust parameters to achieve the desired ablation zone, enhancing its precision while minimizing risks of damaging healthy liver tissue.

#### Data Handling

Data from the participating centres will be split into training, validation, and test sets to evaluate model performance. The training and validation sets will serve model development, including hyperparameter optimization and iterative refinements, while the test set will be held out to provide an unbiased estimate of the final model accuracy. In addition, an external validation cohort from a separate clinical centre will further assess the generalizability of the models.

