### Outcomes

#### Primary Outcomes

The primary outcomes of this registry study are to investigate practice variability and identify best practices, and to develop and validate clinical tools and AI models to optimize treatment planning, tumour targeting, assessment of treatment effect, and outcome prediction in patients undergoing TLA for primary or secondary liver tumours.

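### The validation scheme assigns generalisability to one external centre and, as written, provides no estimate of how AI model performance varies between centres

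*Protocol article*

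**What the plan says.** The Data Handling section of the protocol article sets out validation in three steps.

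- Development and internal testing: "Data from the participating centres will be split into training, validation, and test sets to evaluate model performance".
- The purpose of the test set: "the test set will be held out to provide an unbiased estimate of the final model accuracy".
- Generalisability: "an external validation cohort from a separate clinical centre will further assess the generalizability of the models".

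The number of external centres is therefore given, and it is one. The section does not say whether the first split is by patient or by centre.

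Three other sections give the context. The Introduction says that technical advances have "paradoxically led to greater diversity in workflow practices", and that "data are collected from various centres to gain insight into inter-centre treatment variability and outcomes". The Intervention section lets each treating physician choose the ablation method, device, settings and guidance. It also allows CT or cone-beam CT with intravenous or hepatic-arterial contrast, so the images that feed the models can differ by site. Primary Outcomes includes the aim to "develop and validate clinical tools and AI models to optimize treatment planning".

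Trial Design and Study Setting names two coordinating centres and eight further participating centres, and adds: "Other centres will be welcome and/or invited to participate".

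**The concern.** A model meant for use beyond the centres that built it has to answer two questions. How well does it do, on average, in a centre it has not seen? How much does that vary from one such centre to the next? Where workflow and imaging are expected to differ between centres, the second question matters as much as the first.

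The scheme gives generalisability to a single cohort at a single site. That answers neither question with known precision. It shows how the model did there, and enrolling more patients at that site does not show how the next site would differ. A good result could come from a centre that resembles the training centres, and a poor one from an unusual centre. Nothing in the described scheme would tell these apart.

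At stake is what the validation part of the primary outcome can support. The article's closing section hopes for a workflow that can be adopted anywhere, and a result from one external centre says little about that.

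**Working it through.** **The plan's own figures.** There is no figure to reproduce. Sample Size mentions about 1200 patients for the AI work, with no derivation, and says that the sample size was not predetermined. The argument below does not use that number.

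**Inputs from the article.**
- External centres: 1 (Data Handling).
- Named centres: 2 coordinating + 8 participating = 10 (Trial Design and Study Setting).
- Unit of the train/validation/test split: not stated.

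**Input not in the article (assumption).** Between-centre SD of a performance measure, τ. The values 0.02, 0.05 and 0.08 are used to show a range. They are not estimates for any particular model or metric.

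**Step 1: degrees of freedom.** With k evaluation centres, the between-centre variance has k − 1 degrees of freedom.
- k = 1: 1 − 1 = 0, so τ cannot be estimated. This needs no assumption.
- k = 10: 10 − 1 = 9. From the chi-square distribution on 9 degrees of freedom, the 95% interval for τ runs from about 0.69 to 1.83 times its estimate.

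**Step 2: distance from the average centre, due to between-centre variation alone.** The 95% half-width is 1.96 × τ / √k.

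| τ (assumed) | k = 1 | k = 10 |
|---|---|---|
| 0.02 | 1.96 × 0.02 = 0.039 | 0.039 / 3.162 = 0.012 |
| 0.05 | 1.96 × 0.05 = 0.098 | 0.098 / 3.162 = 0.031 |
| 0.08 | 1.96 × 0.08 = 0.157 | 0.157 / 3.162 = 0.050 |

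The k = 10 column is best-case. It treats τ as known, and it ignores sampling error within centres and the overlap of training sets when centres are left out in turn. With τ estimated on 9 degrees of freedom, the figure for 0.05 becomes 2.262 × 0.05 / √10 = 0.036.

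**Step 3: what ten centres do not change.** The table compares how well the average centre is located. It does not mean that a new centre would vary less. With ten centres and τ = 0.05, the 95% prediction half-width for a new centre is 2.262 × 0.05 × √(1 + 1/10) = 0.119. The spread stays wide; the gain is that it can be estimated and reported. With one centre no such interval can be calculated from the data.

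**Step 4: if the external site is one of the ten.** The article does not say whether it is. If so, nine centres remain: 8 degrees of freedom, half-widths of 0.013 to 0.052 over the same range of τ, and an interval for τ of 0.68 to 1.92 times its estimate. The conclusion is the same.

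**The case against.** A held-out test set followed by external validation is a recognised and defensible plan. The external cohort is introduced as an addition to the test set, not as a replacement for it. The article is condensed, so the split unit, centre-specific calibration and any leave-one-centre-out analysis may be in a fuller document that is not shown. Leave-one-centre-out validation also has limits: it tests refitted models, not the final one, and a small centre may have few early recurrences.

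Most of this stands. In particular, four stronger readings that a reader might infer are not supported:

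- *The test set comes from the same centres as the training data.* The article says only that participating-centre data are split. Division within centres is the natural reading, since the external cohort is contrasted as coming from a separate centre, but a test set of whole centres is not excluded.
- *Transport to new centres cannot be assessed.* The external cohort is a real check at one unseen site, and nothing in the article prevents further analyses by centre.
- *Validation passes or fails on the choice of one centre.* The article sets no threshold for success. Its hope for a universal workflow is a long-term aim, not a conclusion tied to this cohort.
- *Each left-out centre would supply about 120 patients.* That is 1200 / 10 and assumes equal contributions, whereas the article gives no numbers by centre and does not say what data each centre already holds.

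What the objection does not remove is that the number of external centres is a stated choice, not a detail left to another document, and that this one centre is the only component the article assigns to generalisability.

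**Conclusion.** The point holds in a limited form. The article fixes one external centre and leaves the unit of the main split open. As written, it therefore provides one check of transport to one new site and no estimate of between-centre variation in model performance. That fits poorly with a registry founded on between-centre variation whose primary outcome includes validating the models.

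The absence of any degrees of freedom for the spread is certain and rests on no assumption. The numerical size is illustrative: for an assumed between-centre SD of 0.02 to 0.08, one centre may lie about 0.04 to 0.16 from the average centre, against about 0.01 to 0.05 for a mean over ten centres in the best case. The planned test set and external cohort remain useful. The conclusion is that an inexpensive and better scheme is available and should be adopted, preferably before the models are tuned.

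**What to change.** Revise the Data Handling section as follows:

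1. State whether the training, validation and test sets are divided by patient or by centre.
2. Add internal-external (leave-one-centre-out) validation across the participating centres, at least for the early-recurrence model and, where computing allows, for the segmentation models.
3. Report performance for each left-out centre, plus calibration for the prognostic model, together with the between-centre spread and its uncertainty.
4. Keep the separate external centre as a further check, and limit the conclusion drawn from it to that centre.

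**Cost.** More computing and a rewritten paragraph; the analysis uses data that the named centres are to contribute, so it needs no additional patients or images. Small centres will give imprecise estimates and may have few recurrence events. The refitted models will not be identical to the final model, so their results describe the modelling procedure rather than the released version. The headline accuracy will probably be slightly lower.
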